### Interventions

#### *Control arm*

Patients in the control arm will receive at least six courses of platinum-containing chemotherapy. The first course should be given as soon as possible but within 4 weeks after randomisation. Chemotherapy dose and schedule, combination with other chemotherapeutic agents and pre-and post-chemotherapy medication and hydration is left to the discretion of the participating center. Before every chemotherapy cycle, hematological, renal, and hepatic function will be determined and toxicity is scored using the common toxicity criteria for adverse effects (CTCAE) version 4.0.

#### *Experimental arm*

Secondary cytoreductive surgery must be performed within 4 weeks after randomisation. All patients will be prepared for the possibility of a bowel stoma. Surgery is carried out under antibiotic prophylaxis. The combination of antibiotics will be according local standards. The objective of the surgical intervention is complete resection of all visible disease. The extensiveness of surgery is left to the discretion of the gynaecological oncologist. The surgical procedure should start with obtaining a peritoneal fluid sample for cytology. Patients who have at least 500 ml of peritoneal fluid at the time of laparotomy are considered positive for ascites. To gain proper insight in the tumor spread, all adhesions from any previous surgery have to be excised. This is followed by a thorough inspection and palpation of the intra-abdominal and retroperitoneal contents. The extend of tumor growth is carefully recorded in eight abdominal regions. In case of peritonitis the number of tumor deposits will be recorded. Based on this information, a plan for dissection is made. At the end of the cytoreductive procedure, the extensiveness of surgery, duration of the operation, the amount of blood loss and the amount of residual tumor is recorded. Secondary cytoreductive surgery is considered complete if there is no tumor left, optimal if the largest residual tumor is ≤ 1 cm and suboptimal if more than 1 cm residual tumor (diameter (length, width or depth) of the separate tumor depositions) is left. The first chemotherapy course should be given as soon as possible but within 6 weeks after surgery.

### Post-treatment evaluation

In both treatment arms, evaluation of response will take place before the fourth chemotherapy course and within six weeks after the sixth chemotherapy course. This evaluation consists of determining CA 125 (GCIG criteria) and performing a CT-scan (RECIST 1.1). Toxicity is scored using the common toxicity criteria for adverse effects (CTCAE) version 4.0. Patients will be asked to fill out a quality of life questionnaire (EORTC QLQ-C30 version 3.0 and QLQ-OV28, EQ-5D). After cytoreductive surgery in the experimental arm, haemoglobin must be determined. A Case Report Form (CRF) with respect to the chemotherapeutic treatment and operation must be completed.

### Follow-up

As the primary outcome measure of this study is progression free survival, strict follow-up is warranted. After completion of therapy, the patients will be evaluated by their gynaecological oncologist/gynaecologist and medical oncologist every three months for the first two years and twice annually during the third, fourth and fifth year. At each outpatient control, patient’s history need to be obtained and CA 125 will be determined. A CT-scan has to be performed if there are clinical symptoms and CA 125 is in the normal range (0-35 U/ml) or if CA 125 is increased according to the GCIG criteria and there are no clinical symptoms. As overall survival is one of the secondary endpoints, follow-up of each patient in the study will be at least three years with a maximum of five years. Any treatment for second, third or later recurrence has to be documented. All data will be registered on a follow-up Case Record Form (CRF).

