### Statistical analysis

#### *Sample size*

Progression free survival of patients in the control arm is estimated at ten months. An increase in progression free survival of at least five months in favor of the experimental treatment is considered acceptable given the expected surgery related morbidity. To detect a constant hazard ratio of 1.5 with a 0.05 two-sided significance level and a power of 80%, 104 patients should be enrolled in each arm. Assuming an accrual period of five years, three years of follow-up and 10% loss to follow up, 230 patients need to be included.

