### Interim analysis

An interim analysis for efficacy is planned at two months after randomisation of the last patient. Whatever the outcome of the interim analysis, all randomised patients will be followed until 36 months after randomisation of the last patient. This means that even in case of a statistically significant treatment effect, the trial will not be stopped. The objective of this interim analysis is that patients who are not participating in this study might profit in case of early positive results. The Peto-Haybittle rule, that requires P <0.001 as evidence, will be applied. This leaves the significance level of the final primary efficacy analysis at 0.0498.

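### The five-year maximum on each patient's follow-up conflicts with the common end date 36 months after the last randomisation; the cost is some precision for overall survival, not for the primary endpoint

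*Protocol article*

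**What the plan says.** Three sections of the protocol article bear on how long a patient is followed.

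- **Follow-up** sets a range for each patient and links it to overall survival being a secondary endpoint: "follow-up of each patient in the study will be at least three years with a maximum of five years". Its visits are counted from the end of treatment and stop with year five: "every three months for the first two years and twice annually during the third, fourth and fifth year".
- **Interim analysis** sets a calendar end that applies whatever the interim result: "all randomised patients will be followed until 36 months after randomisation of the last patient".
- **Sample size** rests on "Assuming an accrual period of five years, three years of follow-up and 10% loss to follow up".

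No section says which rule governs the final data set. The Follow-up section does not say whether its five-year maximum runs from randomisation or, like the visits, from the end of treatment.

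**The concern.** The first patient enters at month 0 and the last at month 60. A common end 36 months after the last entry gives follow-up of 36 to 96 months, whereas a five-year maximum stops it at 60. The two rules would agree only if accrual took 60 − 36 = 24 months or less, and the article assumes 60.

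What is at stake is the information available for overall survival. Any death between a patient's fifth anniversary and the common end date counts under one rule and is censored under the other. The Follow-up section gives overall survival as the reason for the length of follow-up, yet its maximum is what removes these deaths. If the choice between the rules were left until results were known, it would also be open to challenge.

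**Working it through.** **Inputs from the article.** Accrual 60 months, further follow-up 36 months, 104 per arm before loss and 230 in total, 10% loss, hazard ratio 1.5, two-sided 0.05, 80% power (Sample size). Control PFS: "Progression free survival of patients in the control arm is estimated at ten months". Gain: "An increase in progression free survival of at least five months in favor of the experimental treatment" of at least five months, so medians of 10 and 15 months. Final significance level 0.0498 (Interim analysis). Overall survival medians on chemotherapy of 18, 29 and up to 35 months (Background).

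**Assumptions.** Exponential survival; uniform accrual; cap counted from randomisation unless stated; no dropout unless stated.

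**Formulas.** With L = ln 2 / median:

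- Event probability, common cut-off: 1 − [exp(−36L) − exp(−96L)] / (60L)
- Event probability, cap at c months: 1 − { [(96 − c)/60]·exp(−cL) + [exp(−36L) − exp(−cL)] / (60L) }
- Power with d events: Φ( (√d / 2)·ln 1.5 − z ), where z is the two-sided critical value

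**1. The plan's own figure.** Freedman's formula requires 197 events and Schoenfeld's 191.

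- Common cut-off: event probabilities 0.9805 (median 10) and 0.9359 (median 15), sum 1.9164. Freedman gives 197 / 1.9164 = 102.8 per arm; Schoenfeld gives 191 / 1.9164 = 99.7.
- 60-month cap: 0.9746 and 0.9167, sum 1.8913. Freedman gives 197 / 1.8913 = 104.2 per arm; Schoenfeld gives 191 / 1.8913 = 101.0.

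The stated 104 is matched closely by Freedman's formula under either rule, so it does not show which rule was meant. For the total, 208 × 1.10 = 228.8 and 208 / 0.9 = 231.1; the stated 230 lies between.

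**2. Who is affected.** Patients entered in the first 36 of 60 months, 36/60 = 60% or about 138 of 230, entered early enough to reach the cap before the common end date. The share still at risk there is 0.6 × exp(−60L):

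- Progression-free: 115 × 0.6 × 0.0156 = 1.1 in the control arm and 115 × 0.6 × 0.0625 = 4.3 in the experimental arm, about 5 of 230 (2%).
- Alive, per arm of 115: 6.8, 16.4 and 21.0 at medians of 18, 29 and 35 months (6%, 14% and 18%).

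**3. Events lost to a 60-month cap.** All rows use 230 patients; the overall survival rows use the same median in both arms.

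| Endpoint | Common cut-off | Cap | Lost |
|---|---|---|---|
| PFS, medians 10 and 15 | 220.4 | 217.5 | 2.9 (1.3%) |
| Deaths, median 18 | 207.6 | 201.3 | 6.3 (3.0%) |
| Deaths, median 29 | 178.3 | 167.5 | 10.8 (6.1%) |
| Deaths, median 35 | 164.0 | 152.0 | 12.0 (7.3%) |

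With 207 evaluable patients (230 × 0.9) every count falls by a tenth and the percentages do not change; PFS becomes 198.3 versus 195.7 events.

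**4. Power.** PFS at level 0.0498 with 230 patients: 85.3% versus 84.8%. For overall survival the article states no effect size. If a hazard ratio of 1.5 is assumed at level 0.05, power falls from 80.9% to 79.2% at a control median of 18 months, from 73.4% to 70.1% at 29, and from 69.3% to 65.5% at 35.

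**5. Sensitivity.**

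- Five years counted from the end of treatment, taken as about six months after randomisation (an assumption), gives c = 66. Then (96 − 66)/60 = 50% entered early enough. PFS events are 220.4 versus 218.8 (1.6 lost). With equal medians, deaths are 207.6 versus 203.9, 178.3 versus 171.5 and 164.0 versus 156.4, a loss of 1.8%, 3.8% and 4.7%.
- Constant dropout of 10% per five years, with c = 60, gives 214.5 versus 211.9 PFS events. With an assumed hazard ratio of 1.5, it gives 188.2 versus 180.9, 155.2 versus 144.9 and 140.8 versus 129.8 deaths. The losses are about the same size.

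**The case against.** The best case for leaving this alone is that it does not matter to the trial's main question. PFS is primary, few patients are progression-free at five years, and power moves by half a point. Overall survival is secondary and has no stated power. A five-year maximum is in itself a defensible choice and lies well beyond every chemotherapy median that the article cites. A fuller protocol stands behind the article. Most of this is right, and it limits the size of the point. It does not remove the contradiction: the article affirms both rules, the calendar rule covers every randomised patient, and counting from the end of treatment narrows the conflict without resolving it.

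A reader might infer more than the article supports:

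- **That 60% of patients are cut short.** That is the share entered early enough. About 2% would be progression-free, and 6% to 18% alive, when the cap takes effect.
- **That the treatment comparison would be biased.** A cap fixed by date and applied alike in both arms is administrative censoring. It costs precision and leaves the planned Kaplan-Meier and log-rank analyses valid.
- **That a late benefit of surgery would be missed.** The article gives no ground for expecting a benefit confined to the period after year five.
- **That centres will apply different rules.** The text allows it, but nothing shows that it will happen.

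**Conclusion.** The inconsistency is real. With 60 months of accrual, the five-year maximum and the common end date cannot both hold for patients entered in the first 36 months who are still alive or progression-free at five years.

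Its consequence is modest. The cap would cost about 1% of PFS events, leaving the sample size and the primary analysis essentially untouched. It would cost about 3% to 7% of deaths at medians of 18 to 35 months, or about 2% to 5% if the clock starts about six months after randomisation. These sizes rest on exponential survival, uniform accrual and medians that the article cites for chemotherapy. The two- to four-point fall in overall survival power rests further on an assumed hazard ratio. The point deserves correction because overall survival is a named secondary endpoint and the correction is cheap, not because the primary conclusion is at risk.

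**What to change.** Reconcile the Follow-up and Interim analysis sections by stating one end of follow-up, and the date from which it is counted, separately for PFS and for survival status. PFS is defined from randomisation, so the same origin would keep the clock consistent with the endpoint.

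The option that fits Sample size and Interim analysis is to replace the five-year maximum by the common cut-off 36 months after the last randomisation, at least for survival status. Periodic status checks after year five would be enough for this. Because the PFS loss is about 1%, extending progression assessment beyond year five is optional. If the sponsor prefers the five-year maximum, the Interim analysis text should be changed to match and the loss of deaths accepted openly.

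The cost is a change of wording. Under the common cut-off there is also a small amount of extra data collection on early entrants still alive after five years: about 7 to 21 patients per arm in the model above.

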#### *Quality of life*

Health-related quality of life (HRQL) is one of the secondary endpoints in this study. It will be assessed with self-reported questionnaires (EORTC QLQ-C30 version 3.0 and QLQ-OV28, EQ-5D) to evaluate the impact of secondary cytoreductive surgery added to platinum based chemotherapy. The questionnaires have to be filled out after the sixth chemotherapy cycle and at 3, 6, 9, 12, 18 and 24 months following treatment.

#### *Assessment of serious adverse events*

A serious adverse event (SAE) related to surgery and/or chemotherapy will be collected and recorded on the Serious Adverse Event Report Form during every trial phase. They all must be reported to the principal investigator within 24 hours and will be followed until they have abated or until a stable situation has been reached.

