## Methods/Design

### Study design

This study is a multicenter prospective randomised controlled phase III trial in which all nine Dutch gynaecological oncology centres and affiliated hospitals are participating. Patients with first recurrence of platinum-sensitive epithelial ovarian cancer, primary peritoneal cancer or fallopian tube cancer will be randomly assigned to the control arm and experimental arm in a 1:1 ratio. In the control arm patients receive the standard treatment for platinum-sensitive recurrent ovarian cancer of at least six cycles of intravenous platinum containing chemotherapy. In the experimental arm treatment consists of secondary cytoreductive surgery followed by at least six cycles of intravenous platinum containing chemotherapy (Figure 1).

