### Safety reviews and monitoring

The SOCceR study has established an Independent Data Safety Monitoring Board (DSMB) comprising of independent experts who have no conflict of interest and agree with the outline of the protocol. The committee will meet once a year. Following this meeting, the DSMB will report to the Study Coordinators about (serious) adverse events, whether or not recruitment is on target and the compliance with the QoL assessments is adequate. The committee may recommend changes in the conduct of the trial and exclusion of a single center if excessive rates of morbidity are present. All data presented at this meeting will be considered confidential. During the study, the committee may decide to change the frequency of discussion.

Safety reviews are planned primarily to guard against unfavorable results in the experimental arm. Death and failure rates and SAE reports for both treatment arms will be closely monitored in order to pick up any (unexpected) trends. Safety reviews will be presented confidentially to the DSMB every six months, and/or at request of the DSMB. These biannual reviews will include data on number and causality of deaths, number of treatment failures and serious adverse events. The DSMB can recommend to modify or stop the study prematurely, if number and causality of deaths, number of treatment failures and serious adverse events are significantly greater than was foreseen in the literature. The assessment of the DSMB, will be presented to the principal investigators and will be reported in the annual progress report to the accredited Medical Ethics Committee.

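### SAEs are collected only if related to surgery or chemotherapy, and surgery is given in one arm only, so the SAE reports the DSMB sees may be filtered differently by arm

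*Protocol article*

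**What the plan says.** All references are to the protocol article.

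- **Assessment of serious adverse events:** "A serious adverse event (SAE) related to surgery and/or chemotherapy will be collected and recorded". The rule covers every phase of the trial. The next sentence, "They all must be reported to the principal investigator within 24 hours", applies to the events so collected. The section does not say who decides relatedness or by what criteria.
- **Study design:** "In the experimental arm treatment consists of secondary cytoreductive surgery followed by at least six cycles of intravenous platinum containing chemotherapy". For the comparator: "In the control arm patients receive the standard treatment for platinum-sensitive recurrent ovarian cancer of at least six cycles of intravenous platinum containing chemotherapy". Surgery as a trial treatment therefore exists in one arm.
- **Control arm:** "The first course should be given as soon as possible but within 4 weeks after randomisation".
- **Experimental arm:** "Secondary cytoreductive surgery must be performed within 4 weeks after randomisation". Chemotherapy then starts within 6 weeks after surgery.
- **Safety reviews and monitoring:** SAE reports from both arms are watched for trends, including unexpected ones, mainly to protect patients in the experimental arm. "These biannual reviews will include data on number and causality of deaths, number of treatment failures and serious adverse events". The DSMB may recommend changing or stopping the study if deaths, treatment failures and SAEs clearly exceed what the literature foresaw.

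**The concern.** Relatedness is a judgement. When it is used as an entry condition, the events judged unrelated leave no SAE record that could be reviewed later. That is tolerable if the judgement works alike in both arms. Here it has two named treatments to attach to in one arm and one in the other. The treatments also cannot realistically be concealed from the site, since one arm has an operation and the other does not.

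What is at stake is the DSMB's monitoring. It is asked to notice unexpected trends, and an unexpected harm is the kind least likely to be called related when it occurs. A comparison of all SAEs between arms can show such a harm even when nobody suspects the cause. A comparison of events already screened for cause may not. The Background section itself says that information on morbidity from this surgery is scarce, so the trial has good reason to collect these events fully.

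**Working it through.** The article gives no SAE rate and no attribution rate, so there is no stated figure to reproduce on this point. The first step compares the rules by period. The second is an illustration on assumed rates.

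**1. Routes onto the SAE form**

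| Period | Control arm | Experimental arm |
|---|---|---|
| Randomisation to first trial treatment (up to 4 weeks in each arm) | none | none |
| Surgery to first chemotherapy course (up to 6 weeks) | no such period | related to surgery |
| From first chemotherapy course | related to chemotherapy | related to surgery or to chemotherapy |

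The wait for first treatment has the same upper limit in both arms. The asymmetry starts at the operation. From then until chemotherapy, for up to 6 weeks, the experimental arm has an open route. A control patient still awaiting the first course has none. Once chemotherapy has begun both arms have a route, but the experimental arm keeps the additional one.

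**2. Other safety data that could fill the gap**

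- *Deaths.* The primary outcome counts death from any cause, and the DSMB sees number and causality of deaths. This covers fatal events only.
- *CTCAE toxicity.* It is scored before each cycle (stated under Control arm) and, in both arms, before the fourth course and within six weeks after the sixth. No relatedness limit is stated. Scoring before a control patient's first course might note an event from the waiting period. But the scoring follows the chemotherapy timetable, is analysed after the third and sixth courses, and is not named among the data for the six-monthly reviews. It is not listed for the follow-up visits.
- *Surgical morbidity at 30 days.* Descriptive, tied to the operation, with no counterpart in the control arm.
- *Hospital records.* Under Quality assurance, records that allow linkage to hospital files are kept for 15 years. This permits recovery afterwards, not at the time of a review.

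**3. What a filter could do (assumed rates, none from the documents)**

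Patients per arm: 230/2 = 115. Recorded rate = true SAE risk × share called related.

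*A false difference.* Take a true risk of 30% in both arms, with 50% called related in the control arm and 80% in the experimental arm:

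- recorded rates: 0.30 × 0.50 = 0.15 and 0.30 × 0.80 = 0.24
- expected patients: 115 × 0.15 = 17.3 and 115 × 0.24 = 27.6
- pooled rate 0.195; SE0 = √(2 × 0.195 × 0.805/115) = 0.0523
- SE1 = √((0.15 × 0.85 + 0.24 × 0.76)/115) = 0.0519
- chance of a nominally significant excess (two-sided 5%) = Φ((0.09 − 1.96 × 0.0523)/0.0519) = Φ(−0.24), about 41%

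The same formula over a range, with 50% of control SAEs called related throughout:

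| True risk, both arms | Experimental share 50% | 60% | 70% | 80% | 90% |
|---|---|---|---|---|---|
| 20% | 2.5% | 7% | 15% | 27% | 42% |
| 30% | 2.5% | 9% | 22% | 41% | 61% |
| 40% | 2.5% | 11% | 29% | 55% | 78% |

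*A hidden difference.* Take a true risk of 20% in the control arm and 40% in the experimental arm, with 80% and 40% called related. Recorded rates are 0.20 × 0.80 = 0.16 and 0.40 × 0.40 = 0.16. A true doubling, 23 against 46 patients of 115, appears as no difference.

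**The case against.** The strongest case against runs as follows.

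- *The only arm-level use of SAEs is the DSMB's monitoring.* This stands. Under Data analysis the formal between-arm test is on toxicity proportions. A reader might infer that a planned SAE comparison is biased, but no such test is planned.
- *No judge is named.* This stands. A reader might infer that an unblinded investigator decides relatedness. That is plausible, because the arm can hardly be hidden, but the text does not say it. Who decides may properly sit in the full protocol. The restriction itself, however, is stated in the article.
- *The five-month target does not use these counts.* This stands. The statement under Sample size about expected surgical morbidity is a design-stage judgement, made before any SAE is recorded.
- *Over-attribution to surgery would only make the DSMB more cautious, and its stopping criterion refers to the literature.* Partly right. Under-attribution would weaken the protection, nothing in the rule prevents it, and the DSMB is also asked to follow both arms for unexpected trends. An external benchmark does not help if the trial's own count is incomplete.
- *Recording postoperative SAEs is what the rule is for.* True, and not a fault. The fault is that comparable events in the other arm are not recorded.
- *Surgery is not defined in the rule, and a diagnostic laparoscopy is allowed when eligibility is assessed.* A control patient could therefore occasionally have a surgery-related event. The procedure is optional and precedes randomisation, so it does not restore balance.

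**Conclusion.** The point holds as a defect in how safety data are collected. Followed as written, the rule gives the DSMB SAE reports that can be filtered differently by arm, most clearly between surgery and chemotherapy. It also tends to leave out harms that nobody yet suspects. This rests on the wording of the rule, on surgery being given in one arm, and on the inference that sites know the arm.

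The size and the direction cannot be derived from the documents. The table shows only that moderate attribution gaps could matter: at 30% true risk, a spurious significant excess has a 9% chance with a ten-point gap and 41% with a thirty-point gap. These figures depend wholly on the assumed rates and do not predict what will happen in this trial.

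A reader might conclude that the loss is beyond repair. The documents do not support that. Any-cause deaths, toxicity scores and linkable hospital records would recover part of it. Recovery would be incomplete for non-fatal events and too late for the six-monthly reviews. The primary endpoint, significance level and sample size are unaffected.

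**What to change.** 1. Reword the rule so that every SAE in both arms is collected from randomisation to a fixed time after last treatment, with relatedness to surgery and to chemotherapy recorded as fields on the form.
2. Show the DSMB all SAEs by arm first and related SAEs second. Give time at risk alongside: the experimental arm can take up to 4 + 6 = 10 weeks to reach chemotherapy against 4 in the control arm, so its collection window may be up to 6 weeks longer.
3. If the workload needs limiting, exempt only categories that require no causal judgement, such as planned admissions. Exempting disease progression would bring the same judgement back for events such as bowel obstruction.
4. For patients already randomised, retrieve unreported SAEs from hospital records and mark them as collected retrospectively.

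If the full protocol already collects all SAEs, only the article's sentence needs correcting. Otherwise the cost is a change of wording, a modest increase in SAE forms across 230 patients, and some retrospective retrieval.
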